#### Blood Collection and DNA Extraction

Approximately 5 milliliters of blood will be collected into ethylenediaminetetraacetic acid (EDTA) containers for genetic analysis. The blood samples will be transported to the laboratory under a cold chain. Immediately after collection, the genomic DNA will be extracted using the QIAamp DNA blood kit (Qiagen). The extracted DNA will be checked for purity using an ultraviolet spectrophotometer and the integrity will be checked by running the genomic DNA on a 2% agarose gel using triacetate-EDTA buffer in parallel with DNA ladders (all procured from Vivantis Sdn Bhd Malaysia). The genomic DNA with high quality will be stored at –20 °C pending genetic analysis.

#### VDR Genotyping

The polymerase chain reaction–high-resolution melting (PCR-HRM) technique will be used to amplify the VDR gene with specific primers. The amplified region of the VDR gene (amplicon) will be stored in a PCR tube. Sets of primers (procured from Apical Scientific and Biotechnology Sdn Bhd Malaysia) spanning the 5′-3′ region of the *VDR* sequence will be synthesized based on published sequences [24], which will be used to run the PCR-HRM analysis to detect *VDR* variants. The extracted DNA will be subjected to PCR-HRM following the manufacturer’s protocol using the cycling conditions based on a previous report [24].

#### Principle of PCR-HRM

PCR-HRM analysis is a sensitive and specific technique for the detection of mutations on double-stranded DNA (dsDNA) samples (amplicons). First, the region of interest on the DNA is amplified in real time using specific primers prior to the HRM phase. The HRM process then begins with slow denaturation of the dsDNA with a temperature range of 50-95 °C in conjunction with an intercalating fluorescent dye, SYBR Green (Roche). When the melting temperature of the dsDNA is reached, the two strands “melt” apart. The midpoint of the melt curve is described as the point when 50% of the DNA is double-stranded and 50% is single-stranded. The shape of the curve is dependent on the characteristics of the dsDNA, which relate to whether it is the homozygous wild-type, homozygous mutant, or heterozygous wild-type and mutant genotype. When the two strands “melt” apart, the fluorescence level drops. As the HRM is monitored in real time, this curve offers a real-time picture of the characteristics of the DNA being tested.

#### Barcode-Tagged Sequencing Analysis

Barcode-tagged sequencing (BT-Seq) analysis, as a next-generation sequencing approach, will be used to verify the *VDR* SNVs identified among the Malay pregnant women with vitamin D deficiency and HDP according to the PCR-HRM results. BT-Seq services will be sought from TreeCode Sdn Bhd Malaysia. Ten amplicon samples will be selected from each of the identified *VDR* variants as representative samples to serve as the reference genotype for all SNVs detected in the PCR-HRM analysis. The analysis will be performed on each *VDR* variant amplicon that will be synthesized based on published primers spanning the four known VDR SNVs (*BsmI, ApaI, TaqI,* and *FokI*) using PCR [24]. The amplicons will be run on an agarose gel and the purified products will be cut from the gel before sending to the company providing the BT-Seq service. Discrimination of the three possible genotypes of each genetic variant (common homozygotes, heterozygotes, and rare homozygotes) in 4 distinct groups will be obtained from 180 samples by PCR-HRM analysis. A T-to-C transition in introns 8 and 9 will reflect the presence of SNVs in introns 8 and 9 for *BsmI* and *TaqI*, respectively; a C-to-T transition at the junction of intron 1 and exon 2 reflects the *FokI* variant; and the *ApaI* variant is reflected by a T-to-G transition in intron 8. The corresponding distribution of vitamin D status and the genotype frequency in Hardy-Weinberg equilibrium will be obtained for each SNV.

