**Methods:**

This prospective study consists of two phases. The first phase is a cross-sectional study that will entail gathering medical records, a questionnaire survey, and laboratory testing for vitamin D status, with a planned recruitment of 414 pregnant women. The questionnaire will be utilized to assess the risk factors for vitamin D deficiency. The vitamin D status will be obtained from measurement of the vitamin D (25-hydroxyvitamin D_3_) level in the blood. The second phase is a case-control study involving a Malay ethnic cohort with vitamin D deficiency. Participants will be divided into two groups with and without HDP (n=150 per group). Genomic DNA will be extracted from the peripheral blood monocytes of participants using the Qiagen DNA blood kit, and *VDR* sequence variants will be determined using polymerase chain reaction–high-resolution melting (PCR-HRM) analysis. Sanger sequencing will then be used to sequence randomly selected samples corresponding to each identified variant to validate our PCR-HRM results. The *VDR* genotype and mutation frequencies of *BsmI*, *ApaI, TaqI,* and *FokI* will be statistically analyzed to evaluate their relationships with developing HDP.

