### Sample Size Estimation

#### Total Sample Size

A total of 414 pregnant women will be recruited for the cross-sectional study (phase 1) to determine the prevalence of vitamin D deficiency and associated risk factors (objective 1). For phase 2, a total of 150 Malaysian pregnant women with HDP will be recruited as the case group and 150 normotensive Malaysian pregnant women with vitamin D deficiency will be recruited as controls.

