### Data Analysis Plan

Data obtained from the study will be analyzed using SPSS version 27.0 (IBM Corp). Data entered will be checked for missing or suspicious values. These will subsequently be verified with the participants or omitted as missing values. Descriptive analysis will be used to summarize the sociodemographic data, anthropometric data, clinical data, vitamin D dietary intake, sun exposure, and physical activity. The prevalence of vitamin D deficiency will be expressed in frequency and percentage. The association with sociodemographic data will be analyzed using the *χ*^2^ test, independent *t* test, and ANOVA where applicable.

We will report the comparative prevalence of *BsmI*, *ApaI, TaqI,* and *FokI*
*VDR* genotypes among Malay pregnant women with vitamin D deficiency with and without HDP. Similarly, the distributions of *VDR* genotype and allele frequencies according to vitamin D deficiency among Malay pregnant women will be reported as a descriptive analysis. Any mutations found in the *BsmI*, *ApaI, TaqI,* and *FokI* VDR gene fragments among Malay pregnant women with HDP will also be described. The associations of vitamin D status, associated risk factors, and VDR genetic variants with HDP will be determined using multivariate logistic regression analysis. The level of significance will be considered at a threshold of *P*≤.05 at the 95% CI.

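### The genotyping text counts 180 samples where Phase 2 plans 300 women, and nothing in the article reconciles the two

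*Protocol article*

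**What the plan says.** **Number of women.** The abstract's Methods paragraph says "Participants will be divided into two groups with and without HDP (n=150 per group"). Total Sample Size gives the same number of cases: "a total of 150 Malaysian pregnant women with HDP will be recruited as the case group". For the other arm, the section states that "150 normotensive Malaysian pregnant women with vitamin D deficiency will be recruited as controls".

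**Who is genotyped.** VDR Genotyping sets no limit: "The extracted DNA will be subjected to PCR-HRM following the manufacturer’s protocol". The Data Analysis Plan compares genotypes "among Malay pregnant women with vitamin D deficiency with and without HDP", that is, across both arms.

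**The conflicting figure.** Barcode-Tagged Sequencing Analysis says that the genotype discrimination "in 4 distinct groups will be obtained from 180 samples by PCR-HRM analysis". It gives no derivation, no case/control split and no selection rule for the 180.

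**Sequencing check.** The same section uses BT-Seq to verify variants "identified among the Malay pregnant women with vitamin D deficiency and HDP according to the PCR-HRM results". It then takes ten amplicons per identified variant as representative samples, to act as the reference for all variants detected by PCR-HRM. The abstract describes the step differently: "Sanger sequencing will then be used to sequence randomly selected samples corresponding to each identified variant".

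**The concern.** The genotype is the exposure in Phase 2, and objectives 2 to 4 all depend on it. The only sentence that counts the samples from which genotypes come gives 180, which is 120 fewer than planned recruitment. This is not a detail left to a fuller document: the article states a number, and that number conflicts with its own sample size.

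Two things are at stake. If 180 is followed, the genetic comparison runs on 60% of the planned women, with less power than the sample size section sets out to secure. In addition, with no stated rule for choosing the 180 or dividing them between cases and controls, selection into the genetic analysis would be undefined.

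A smaller matter sits in the same text. The validation step has two method names and two descriptions of how samples are picked, and one sentence mentions only women with both deficiency and HDP.

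**Working it through.** **1. Inputs from the article**
- Planned: 150 cases and 150 controls (abstract; Total Sample Size).
- Genotyped: 180 (Barcode-Tagged Sequencing Analysis).
- P1 = 0.21, P2 = 0.11, P* = 0.10, r = 1, Z values 1.96 and 0.84, attrition 10% (Sample Size Determination for the Case-Control Study).

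**2. The plan's own figure**

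Equation 2 with r = 1: n = 2 × 0.1 × 0.9 × (0.84 + 1.96)² / 0.1² = 141.12. The stated 141 per group reproduces. (The step from 141 to 150 is a 6.4% increase, whereas 141 × 1.1 = 155.1. That is separate from this point.)

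**3. Can 180 be derived?**

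| Candidate | Count | Gap to 180 |
|---|---|---|
| Planned recruitment, 150 + 150 | 300 | 120 (40.0% of 300) |
| Before attrition, 141 + 141 | 282 | 102 (36.2% of 282) |
| 300 less 10% attrition | 270 | 90 (33.3% of 270) |
| Sequencing, 10 × 4 variants × 3 genotypes | 120 | 60 short of 180 |
| Sequencing, 10 × 4 variants | 40 | 140 short of 180 |

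None gives 180. The sentence also names PCR-HRM, so 180 is not presented as a sequencing count.

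**4. Size of the loss, if 180 were followed**

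Assumption: a 90/90 split, which the article does not state.

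*Article's own equation, solved for power:* Φ(√(n × 0.01 / 0.18) − 1.96)
- n = 150: Φ(2.887 − 1.96) = Φ(0.927) = 82.3%
- n = 90: Φ(2.236 − 1.96) = Φ(0.276) = 60.9%

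*Standard two-proportion test, mean proportion 0.16:* Φ{[0.10√n − 1.96√(2 × 0.16 × 0.84)] / √(0.21 × 0.79 + 0.11 × 0.89)}
- n = 150: Φ[(1.2247 − 1.0162) / 0.5136] = Φ(0.406) = 65.8%
- n = 90: Φ[(0.9487 − 1.0162) / 0.5136] = Φ(−0.131) = 44.8%

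The two methods differ because the article sets P* to the difference (0.10). With the mean proportion (0.16), equation 2 gives about 211 per group. The relative loss is similar either way: (82.3 − 60.9) / 82.3 = 26%, and (65.8 − 44.8) / 65.8 = 32%.

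**5. The same loss on a genotype scale**

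This is the odds ratio detectable at 80% power by the two-proportion formula. The carrier frequencies in controls are assumed, since the article gives none.

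| Control carrier frequency (assumed) | 150 per group | 90 per group |
|---|---|---|
| 0.11 | 2.43 | 3.04 |
| 0.50 | 1.93 | 2.37 |

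**6. Sequencing text side by side**

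| | Abstract | Barcode-Tagged Sequencing Analysis |
|---|---|---|
| Method | Sanger | BT-Seq, described as next-generation |
| Selection | Random, per variant | Ten per variant, as representative samples |
| Source | No restriction | One sentence refers to women with deficiency and HDP; selection is then by variant |

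**The case against.** **180 may be a leftover number.** The sections on genotyping and data analysis name no subset, and no sentence says that 120 women go without a genotype. This stands. It means that the defect is an unreconciled figure rather than a demonstrated plan to discard data. It does not remove the contradiction, because a reader cannot tell which number governs.

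**The power figures rest on weak inputs.** This also stands. The 90/90 split is assumed. The 21% and 11% are deficiency prevalences in women with and without gestational hypertension, whereas Phase 2 recruits women who are already deficient. The percentages show the effect of a smaller n, not the power of the genotype test. It would also be wrong to say that most of the power is lost: the fall is about a quarter to a third.

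**A stronger reading of the sequencing text.** A reader might infer that only case samples are verified, and hence that genotype errors could differ between cases and controls. The article does not support this. The word only is absent, amplicons are chosen by variant and serve as the reference for all detected variants, and the abstract restricts nothing to cases. One PCR-HRM method is described without distinction by case status, and no rule corrects genotypes in cases alone. Even references drawn wholly from cases would not by themselves make error rates differ by group. What remains is ambiguity about the source of the sequenced samples.

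**Conclusion.** The point holds as an internal contradiction. The article takes genotypes from 180 samples while planning 300 women, and none of its own numbers accounts for the difference. Taken literally, 40% of the planned women would have no genotype. On an assumed equal split, power on the article's own equation would drop from about 82% to 61%, missing its 80% target, and by the standard formula from about 66% to 45%. For assumed control carrier frequencies of 0.50 to 0.11, the detectable odds ratio would rise from 1.93–2.43 to 2.37–3.04.

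That 180 does not match 300 rests on no assumption. The power and odds ratio figures do, and should be read as illustrations.

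The conflict between Sanger and BT-Seq, and between random and representative selection, is real but secondary. Differential genotyping error is not established.

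**What to change.** 1. In Barcode-Tagged Sequencing Analysis, replace 180 with all enrolled Phase 2 participants. If a subset is intended, state its number of cases and controls and how they are selected, and restate the power for that number.
2. Name one sequencing method in both the abstract and the Methods.
3. State that the ten amplicons per variant are drawn at random from cases and controls together. This keeps the random selection that the abstract describes and settles where the samples come from.

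Cost: if 180 is a leftover, item 1 is a wording correction. If it was intended, genotyping everyone adds PCR-HRM runs for women already in the recruitment plan. The number of amplicons sequenced does not change.

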### Sample Size Estimation

#### Total Sample Size

A total of 414 pregnant women will be recruited for the cross-sectional study (phase 1) to determine the prevalence of vitamin D deficiency and associated risk factors (objective 1). For phase 2, a total of 150 Malaysian pregnant women with HDP will be recruited as the case group and 150 normotensive Malaysian pregnant women with vitamin D deficiency will be recruited as controls.

#### Sample Size Calculation for the Cross-Sectional Study (Phase 1)

The sample size for the study was calculated using the following formula [25]:

n = (Z^2^ × p × q)/d^2^
**(1)**

where n is the minimum sample size, Z is the level of significance at the 95% CI (1.96), p is the prevalence rate, q = 1 − p, and d is the tolerable margin of error (5%).

According to Woon et al [26], the prevalence of vitamin D deficiency among Malaysian pregnant women is 42.6%. Applying equation 1, the sample size is calculated as follows:

n = (1.96)^2^ × 0.426 × (1 – 0.426)/(0.05)^2^

n **=** (3.8416 × 0.426 × 0.574)/0.0025 = 376

Therefore, the minimum sample size required for the cross-sectional study after addition of a 10% attrition rate is approximately 414 Malaysian pregnant women.

#### Sample Size Determination for the Case-Control Study (Phase 2)

The minimum number of participants to be recruited in the case-control study was determined using the following formula [27]:

n = r + 1 × P* × (1 – P*) × (Z_β_ + Z_α/2_)^2^/r × (P_1_ – P_2_)^2^
**(2)**

where r is the ratio of cases to controls (1 in this instance given the equal numbers in the two groups), P_1_ is the proportion of exposed individuals in the cases, P_2_ is the proportion of exposed individuals in the controls, P* is the effect size (P_1_ – P_2_), Z_β_ at 80% power is 0.84, and Z_α/2_ is 1.96 for a .05 significance level at the 95% CI.

According to Caccamo et al [6], the prevalence of vitamin D deficiency among women with GH (P_1_) and that among pregnant women without hypertension (P_2_) is 21% and 11%, respectively. Therefore, P* is determined to be 0.1 (0.21–0.11). Applying equation 2, the sample size is calculated as:

n = (1 + 1) × (0.1) × (1 – 0.1) × (0.84 + 1.96)^2^/1 × (0.1)^2^

n = 141

Considering dropout or missing samples, 10% attrition is added to the calculated sample size. Hence, our minimum number of participants in each group (cases and controls) was determined to be 150.

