### Case-Control Study (Phase 2)

#### Participants and Data

For the second phase of the study, we chose to focus on the Malay ethnic group, who make up the majority of the Malaysian population. Pregnant women of Malay ethnicity who are classified in the vitamin D deficiency group in phase 1 of the study will be recruited for phase 2. Those with a nonviable pregnancy or those who received a diagnosis of chronic hypertension prior to the current pregnancy will be excluded. The remaining participants will then be divided into two groups: those with HDP (GH, preeclampsia, eclampsia, HELLP syndrome) and those with blood pressure in the normal range.

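### Phase 2 is sized on the prevalence of vitamin D deficiency, which every participant must have, so nothing in the calculation supports the VDR genotype comparison

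*Protocol article*

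**What the plan says.** The Protocol article sizes Phase 2 in Methods, Sample Size Determination for the Case-Control Study (Phase 2). Equation 2 is a two-proportion formula for a case-control study, in which "P_1_ is the proportion of exposed individuals in the cases" and P2 is the matching proportion in controls. The values inserted are prevalences of vitamin D deficiency: "the prevalence of vitamin D deficiency among women with GH (P_1_) and that among pregnant women without hypertension (P_2_) is 21% and 11%, respectively". With 1:1 allocation, two-sided alpha 0.05 and 80% power, the section arrives at 141 per group, and at 150 after an allowance for attrition.

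Phase 2 enrols as follows (Case-Control Study, Participants and Data): Malay pregnant women "who are classified in the vitamin D deficiency group in phase 1 of the study will be recruited for phase 2". These women are then split by HDP status. The Abstract agrees: "The second phase is a case-control study involving a Malay ethnic cohort with vitamin D deficiency".

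The Objectives section gives Phase 2 objectives 2 to 4, which all concern VDR genotypes, alleles or mutations. The Data Analysis Plan compares the BsmI, ApaI, TaqI and FokI genotypes of deficient women with and without HDP. It also relates VDR variants to HDP by logistic regression, with significance at P≤.05.

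**The concern.** In a case-control sample size, the exposure that defines P1 and P2 must be the one the study compares between cases and controls. Here the calculation uses vitamin D deficiency, while the study compares genotype. The enrolment rule also removes any variation in the exposure that was used.

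What is at stake is how the result is read. The article says its findings will support supplementation tailored to genetic background. A reader who sees 80% power and 150 per group will assume the study was built to detect a relevant genetic effect, and could take a null genotype result as evidence of no association. Nothing in the document says what genetic effect the study can detect.

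**Working it through.** **1. Reproducing the plan's figure.** Inputs from the Phase 2 sample size section: r = 1, P* = 0.21 − 0.11 = 0.10, Zβ = 0.84, Zα/2 = 1.96.

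n = (r + 1) × P* × (1 − P*) × (Zβ + Zα/2)² / [r × (P1 − P2)²]
= 2 × 0.10 × 0.90 × 2.80² / 0.10²
= 141.12

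The stated 141 follows from the stated inputs. The issue is what those inputs measure.

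**2. Applying the enrolment rule to the same quantities.**

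| Quantity | Used for sizing | Under Phase 2 recruitment |
|---|---|---|
| P1, deficient among cases | 0.21 | 1.00 |
| P2, deficient among controls | 0.11 | 1.00 |
| P1 − P2 | 0.10 | 0 |

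The denominator of equation 2 becomes zero, so no sample size can power this contrast.

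**3. Correcting P* does not help.** P* is set to the difference between the proportions, whereas the variance term takes their mean, (0.21 + 0.11)/2 = 0.16. With that value, n = 2 × 0.16 × 0.84 × 2.80² / 0.10² = 210.7, or 211 per group. That is a separate error. The corrected figure would still be the size for comparing deficiency prevalence.

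**4. What 150 per group can detect for genotype.** The document gives no genotype frequency or genetic effect, so the control carrier frequency p2 is an assumption. For an odds ratio OR, the carrier frequency in cases is

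p1 = OR × p2 / (1 − p2 + OR × p2)

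and, with p̄ = (p1 + p2)/2,

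n = [Zα/2 √(2p̄(1 − p̄)) + Zβ √(p1(1 − p1) + p2(1 − p2))]² / (p1 − p2)².

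Example with p2 = 0.30 and OR = 1.96: p1 = 0.588/1.288 = 0.4565, p̄ = 0.3783 and p1 − p2 = 0.1565. Then n = (1.96 × 0.6858 + 0.84 × 0.6768)² / 0.1565² ≈ 149, which matches 150 per group.

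Minimum detectable carrier odds ratio for one variant, 80% power, two-sided test:

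| Assumed control carrier frequency | 150 per group, alpha 0.05 | 150 per group, alpha 0.025 | 135 per group, alpha 0.05 |
|---|---|---|---|
| 0.11 | 2.43 | 2.63 | 2.54 |
| 0.20 | 2.09 | 2.24 | 2.17 |
| 0.30 | 1.96 | 2.09 | 2.03 |
| 0.50 | 1.93 | 2.07 | 2.01 |

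The alpha 0.025 column splits 0.05 between BsmI and FokI, the two variants named in the Introduction's hypothesis. This split is illustrative, since the Data Analysis Plan states P≤.05. The 135 column shows the effect of losing 10% of 150.

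**5. Smaller effects.** For an assumed odds ratio of 1.5 at alpha 0.05, the number needed per group is 911, 535, 425, 388 and 388 at control carrier frequencies 0.10, 0.20, 0.30, 0.40 and 0.50. The corresponding power with 150 per group is 21%, 32%, 38%, 41% and 41%.

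**The case against.** There are four fair points on the other side.

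- **The recruitment text is not uniform.** The Total Sample Size section attaches vitamin D deficiency to the controls only and describes the cases simply as women with HDP. On that reading P1 need not be 100%. The controls are still all deficient, against the 11% used for sizing, so the planned contrast remains impossible.
- **Genotype is not the only analysis.** The logistic regression also includes vitamin D status and other risk factors, and the continuous 25(OH)D level can vary among deficient women. This stands, so genotype is better called the main Phase 2 comparison than the only one. The 150 per group was not derived for those other terms either.
- **Part of the genotype work is descriptive.** Determining frequencies and identifying mutations needs no power statement. The case-control contrast and the regression at P≤.05 do need one.
- **The odds ratios are illustrative.** They rest on assumed frequencies and full recruitment. As of December 2023 the article reports 22 cases and 50 controls, so even the 135 column may prove optimistic. The mismatch itself depends on none of these assumptions.

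The genotype calculation cannot be regarded as detail left to a fuller document, because the article gives a complete justification and it is for the wrong exposure.

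**Conclusion.** The concern holds and should be corrected before the study's power is relied on. The sample size section powers a 21% versus 11% difference in vitamin D deficiency that Phase 2 enrolment reduces to zero, and it contains no genetic input. That conclusion comes from the document alone.

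The size of the consequence depends on assumptions: a carrier (dominant) model, one variant at a time, and control carrier frequencies of 0.11 to 0.50. On those terms, 150 per group has 80% power for odds ratios of about 1.9 to 2.4 or larger at alpha 0.05, and about 2.1 to 2.6 if alpha is shared between two variants. The genotype comparison remains valid as an analysis. What fails is the claim that its power has been established.

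**What to change.** Remove the 21%/11% deficiency prevalences as the basis for Phase 2. Keep 150 per group as a fixed size and replace the calculation with a statement of the minimum detectable odds ratio for BsmI and FokI. Give it over a stated range of control carrier (or allele) frequencies, and name the genetic model, the alpha and any sharing of alpha between variants. Show it for 150 per group and for the number expected after attrition, and update it if recruitment falls short. Describe ApaI and TaqI as exploratory, as the Introduction already suggests. Align the Total Sample Size section with the recruitment text on whether cases must be deficient.

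The cost is one recalculation and a change of wording, with no additional participants or procedures.

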## Results

As of December 2023, a total of 340 subjects have been recruited for the phase 1 study. Preliminary analysis showed that 63% of the participants were vitamin D–deficient. Other analyses are pending. For the phase 2 study, 50 control subjects and 22 case subjects have been recruited to date. We are expecting to complete the recruitment by March 2024 and to complete all laboratory and questionnaire analyses by August 2024.

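### The 80% power stated for phase 2 is unsupported: its 21% versus 11% deficiency inputs conflict with the protocol's own prevalence figures, give about 66% power at 150 per group, and do not size the genotype comparison

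*Protocol article*

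**What the plan says.** In the protocol article, Sample Size Determination for the Case-Control Study (Phase 2) takes its inputs from a cited study of vitamin D deficiency. The value for women with gestational hypertension is P1 and "that among pregnant women without hypertension (P_2_) is 21% and 11%, respectively". The error rates are set by "Z_α/2_ is 1.96 for a .05 significance level at the 95% CI" and "Z_β_ at 80% power is 0.84". The variance term uses P*, which is entered as the difference between the two rates: "Therefore, P* is determined to be 0.1 (0.21–0.11" (closing bracket not reproduced). The result is 141 per group, given as 150 after a 10% allowance for attrition.

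Two other places give a deficiency rate for the population under study. Sample Size Calculation for the Cross-Sectional Study (Phase 1) says that "the prevalence of vitamin D deficiency among Malaysian pregnant women is 42.6" per cent. Results, describing 340 recruits, says that "63% of the participants were vitamin D–deficient".

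The Abstract (Methods) and Case-Control Study (Phase 2), Participants and Data, restrict phase 2 to Malay women found deficient in phase 1. These women are then split by hypertensive disorder in pregnancy (HDP). Objectives assigns the genotype and mutation questions to phase 2. Data Analysis Plan adds one logistic regression of HDP on vitamin D status, risk factors and VDR variants, and does not say which phase supplies the data.

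**The concern.** Two sample-size sections of one article use very different deficiency rates. If the 11% and 21% rates applied to this clinic under one definition, the overall rate would have to lie between them. It could not be 42.6% or 63%. The rates behind the phase 2 size therefore look unsuitable for this population, and the power attached to them is in doubt.

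What is at stake is how a null result is read. Taken at face value, the 80% figure would let a non-significant association, whether of vitamin D status or of a VDR variant with HDP, be presented as evidence that none exists. The calculation does not support that for either comparison.

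**Working it through.** **Inputs from the protocol article.** P1 = 0.21, P2 = 0.11, Z values 1.96 and 0.84, ratio 1:1, 150 per group, 10% attrition (Phase 2 sample size section); 42.6% (Phase 1 sample size section); 63% (Results).

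**1. The plan's own figure.** With r = 1 the equation is n = 2 × P*(1 − P*) × (0.84 + 1.96)² / (P1 − P2)². With P* = 0.10: 2 × 0.10 × 0.90 × 7.84 / 0.01 = 141.1. The printed 141 reproduces, but only with the difference in the variance term.

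**2. Same inputs, mean proportion in the variance term.** P* = (0.21 + 0.11)/2 = 0.16, so n = 2 × 0.16 × 0.84 × 7.84 / 0.01 = 210.7, about 211 per group before attrition.

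**3. Power at 150 per group, 21% versus 11%.**
- Pooled standard error under the null: √(2 × 0.16 × 0.84 / 150) = 0.0423.
- Standard error under the alternative: √((0.21 × 0.79 + 0.11 × 0.89)/150) = 0.0419.
- Power = Φ((0.10 − 1.96 × 0.0423)/0.0419) = Φ(0.41), about 66%.
- If 10% of the 150 are lost, 135 remain and power is about 61%.

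**4. Same method at the article's other rates.** This assumes that 42.6% or 63% applies approximately to normotensive women. The odds ratio implied by the plan's inputs is (0.21/0.79)/(0.11/0.89) = 2.15.

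| Effect held | Controls | Cases | n per group | Power at 150 |
|---|---|---|---|---|
| 10-point gap | 11% | 21% | 211 | 66% |
| 10-point gap | 42.6% | 52.6% | 391 | 41% |
| 10-point gap | 63% | 73% | 341 | 46% |
| Odds ratio 2.15 | 42.6% | 61.5% | about 110 | 91% |
| Odds ratio 2.15 | 63% | 78.6% | 134 | 85% |

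So moving to the higher base rate lowers power if the absolute gap is held, and raises it above 80% if the odds ratio is held.

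**5. Can the share of HDP explain the rates?** Suppose normotensive women are at 11% and every woman with HDP is deficient. An overall 42.6% then needs an HDP share of (0.426 − 0.11)/0.89 = 36%, and 63% needs (0.63 − 0.11)/0.89 = 58%. The Introduction puts preeclampsia, one component of HDP, at 2%–8% of pregnancies. Case mix alone is not a plausible explanation. A different cut-off or source population could be.

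**6. Does any row describe phase 2?** Entry requires deficiency, so the deficiency rate is 100% in both groups and cannot differ. The exposure that can differ is VDR genotype, and the sizing section gives no genotype or allele frequency.

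**7. Attrition.** 141 × 1.1 = 155.1 and 141/0.9 = 156.7. The printed 150 is only 6.4% above 141.

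**The case against.** A reader might infer that the low base rate is what breaks the calculation, and that 41% to 46% is the true power of phase 2. Three arguments count against that reading, and all three stand.

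First, the shortfall does not need the prevalence conflict. It is already there at the plan's own 21% versus 11%, because of the value entered for P*. Second, an odds ratio is the natural effect measure for a case-control study analysed by logistic regression, and at the implied 2.15 the higher base rates give 85% to 91%. Low power follows only if a 10-point gap is carried over, and the protocol does not say which effect it means. Third, phase 2 cannot compare deficiency between groups, so printing 41% to 46% would replace one inapplicable figure with another. Total Sample Size calls only the controls deficient, but the Abstract and the phase 2 eligibility text apply the restriction to both groups.

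It is also fair to say that the rates may not measure the same thing. The 42.6% and 63% cover pregnant women without separation by blood pressure, and 63% is preliminary. Classification of Vitamin D Status sets the study's own deficiency limit at below 30 nmol/L, but no cut-off is given for 42.6%, 21% or 11%. This weakens the word contradiction but does not rescue the claim. If the cited rates rest on another definition, the article does not show that they suit a study using this one.

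In the other direction, Data Analysis Plan does keep vitamin D status as a factor for HDP. Deficient versus non-deficient varies only in phase 1, where women with and without HDP are not recruited 150 to 150, so no row of the table describes that analysis either.

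**Conclusion.** The concern holds in limited form: the 80% power claim is unsupported, for three separate reasons. The inputs conflict with the article's own 42.6% and 63%, subject to the unstated cut-offs and populations. On those inputs as given, the power is about 66% rather than 80%. And the quantity sized is not one that phase 2 can compare.

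The documents do not show that phase 2 is underpowered for its genotype comparison. That power is unknown, because no genotype frequency or target effect is given. Nor do they show that the vitamin D comparison has 41% to 46% power. The range of 41% to 91% across the higher base rates reflects an effect that was never fixed. All power figures assume a two-sided 0.05 test of two independent proportions with no covariate adjustment.

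**What to change.** - Withdraw the 80% claim based on 21% versus 11% deficiency.
- For phase 2, keep 150 per group and state the power, or the odds ratio detectable with 80% power, over an assumed range of VDR genotype or allele frequencies. Label the range as an assumption.
- If the association of vitamin D status with HDP is to be analysed, say that it uses phase 1 data. Give its precision or detectable odds ratio from the phase 1 deficiency prevalence and the actual number of women with HDP.
- State the deficiency cut-off and population behind each cited rate, so that the two sample-size sections can be reconciled.
- Add that a null result will be reported with its confidence interval and not interpreted as no association on the strength of an 80% power claim.

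The cost is a rewritten paragraph and a short recalculation, with no extra enrolment. The stated power may come out less favourable.
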